### Recruitment and participants

We decided to focus all interventions on mothers, because in Dutch households women most often fulfil the role of primary caregiver. Participants were recruited from the general population in four Dutch provinces (Zuid-Holland, Noord-Holland, Gelderland and Utrecht) that are closest to the two universities performing the trial, Leiden University and Wageningen University and Research. Participants were recruited by sending emails with information about the study and a link to the website of the study to mothers of 2–4 month-old infants. Addressees included parents who had signed up for the ‘Nutricia for parents group’ or were parents who had ordered a free gift box containing baby merchandise from ‘WIJ Special Media’. All addressees had indicated that they were interested in receiving information on additional opportunities and/or activities. Names and e-mail addresses were available to only a limited number of researchers, ensuring the privacy of the addressees. Finally, we approached potential participants through handing out brochures at youth health care centers within the vicinity of Wageningen University and Research. We cannot ascertain how many families were invited at the youth health care centers, but the total number of families invited through the two e-mail lists was 5565. A total of 409 families expressed interest in our study, 255 of which fulfilled in- and exclusion criteria (see below) and were randomly allocated to the groups (62.3%; see Fig. 2).

**Fig. 2 Fig2:**
[figure not shown]
Flowchart of the inclusion phase

Families that showed interest in our study received a phone-call from one of our trained researchers/students, explaining the study in detail. Families still expressing interest in the study at the end of the call received a detailed information brochure as well as consent forms. Both mothers and fathers were asked to sign and return the consent forms. After receiving the signed consent forms, mothers were asked to fill out an online screening questionnaire which assessed inclusion criteria. Families had to fulfil the following inclusion criteria: a) first-time mothers; b) healthy term infants (37–42 weeks of gestation); c) planning to start complementary feeding at child age of 4–6 months (families that already started complementary feeding were excluded) and d) sufficient knowledge of the Dutch language to receive advice on complementary feeding in Dutch and to be able to fill out Dutch questionnaires. Mothers with major psychiatric diagnoses (e.g., depression, schizophrenia or borderline personality disorder) were excluded, as these may affect parenting [73]. Following the study protocol of Barends and colleagues [26], families were also excluded when the first-borns were twins or in the case of medical problems in the infants that influence the ability to eat, such as food allergies, swallowing or digestion problems. Finally, for standardization purposes, mothers who were not willing to commit to the outcome of the randomization procedure were excluded, e.g. the child was assigned to a VIPP-FI group, but the mother was objecting to being video-taped. A flowchart of the inclusion phase can be found in Fig. 2.

In total, 255 first-time mothers and their babies were randomly allocated to the various conditions. Directly after randomization, prior to starting the intervention-phase, 12 mother-infant dyads dropped out (for reasons, see Fig. 2). A total of 243 families successfully started the intervention-phase. Mean age of the mothers was 30.4 years (*sd* = 4.7, range 18–44). Concerning educational level, 41.6% of mothers had a lower education (finished high school or vocational school), 38.7% finished higher education (higher vocational school) and 19.8% finished university. The trial was thus successful in including a large group with lower education, which is generally considered a risk factor for having less healthy eating habits [74] and less beneficial parental feeding styles [75]. About 18% of mothers worked fulltime, and 63 worked part-time, and 19% did not have paid work Gender of the child was roughly equally distributed (47.3% boys); mean age of the children at the start of the intervention-phase was 4.68 months (*sd* = .42, range 3.98–6.38 months); median age was 4.57 months.

### Interventions

The specific content and timing of the RVE and VIPP-FI interventions are specified in Table 1. To control for possible placebo-effects due to receiving attention from researchers/interveners, the number of contacts with researchers/interveners and time in between contacts are the same for all conditions. The interventions in all groups as well as the attention control condition is performed by trained researchers or Master’s students in the fields of nutrition or child and family studies. Participants in all conditions are allowed to seek any type of concomitant advice on infant feeding during the trial; to control for potential co-intervention bias we ask participants after the interventions are completed whether they sought advice concerning feeding elsewhere, and if so, where and how often.

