**Methods:**

A four-arm randomized controlled trial (Baby’s First Bites (BFB)) was designed for 240 first-time Dutch mothers and their infants, 60 per arm. In this trial, we compare the effectiveness of (a) a vegetable-exposure intervention focusing on the *what* in complementary feeding; (b) a sensitive feeding intervention focusing on the *how* in complementary feeding, (c) a combined intervention focusing on the *what and how* in complementary feeding; (d) an attention-control group. All mothers participate in five sessions spread over the first year of eating solid foods (child age 4–16 months). Primary outcomes are vegetable consumption, vegetable liking and self-regulation of energy intake. Secondary outcomes are child eating behaviors, child anthropometrics and maternal feeding behavior. Outcomes are assessed before, during and directly after the interventions (child age 18 months), and when children are 24 and 36 months old.

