### Aims and hypotheses

In summary, the *Baby’s First Bites (BFB)* study aims to test whether promoting the *what* and**/**or promoting the *how* of complementary feeding will result in increased vegetable consumption and liking and a better self-regulation of energy intake in infants and toddlers up until the age of 36 months. To this end, we will perform a superiority randomized controlled trial with parallel groups, comparing a) an intervention focusing on vegetable exposure (=what), b) an intervention focusing on sensitive feeding (=how), c) an intervention focusing on vegetable exposure and sensitive feeding (=what and how), and d) a control condition. The interventions will begin when the infant starts receiving complementary food (child age 4–6 months, as recommended by the Dutch Nutrition Center) and continue until the child is 16 months old. We hypothesize that a) all interventions are more effective in improving vegetable consumption and vegetable liking than the control condition without guidance on complementary feeding; b) the sensitive feeding and combined intervention will be more effective in supporting child self-regulation of energy intake than the vegetable exposure or control conditions; and c) the combined intervention is more effective than the other two interventions alone in promoting vegetable intake and vegetable liking. As the inclusion phase of the *BFB* study has already successfully been completed, the present article describes the characteristics of the sample of included participants as well as the design of this ongoing study.

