## All groups/conditions

### Feeding schedule and provision of foods in all groups

Prior to the start of each intervention, all mothers are instructed to give their infant rice-flour porridge with a spoon for at least five days, to accustom the infant to eating food from a spoon [26]. Each intervention starts with providing infants their first bites of complementary foods according to a specific 19-day feeding schedule (see Table 3). The infants in the repeated exposure and combined conditions receive a variety of commercially available jars of vegetable purees, whereas the infants in the VIPP-FI and attention-control condition receive similar jars containing both fruits and a sweet vegetable puree (carrots). During the first two days and the last two days of the feeding schedule, the target and control vegetables (cauliflower and green beans) are provided to infants in all conditions. During these days, families are visited at home by the research team and the feed is videotaped; researchers measure at home how much the child has eaten (see *Measures*). During the other days of the feeding schedule, the mother feeds her child at home without the presence of the researchers. To facilitate compliance to the feeding schedule, mothers receive a printed overview of the feeding schedule indicating which puree to feed their child on each of the 19 days. In addition, each jar of food is labelled with a sticker indicating the day of the feeding schedule.

**Table 3 Tab3:** Feeding schedules used within each intervention group and the control group

	Day																		
Condition	1	2	3	4	5	6	7	8	9	10	11	12	13	14	15	16	17	18	19
RE and COMBI	TV	CV	TV	V1	TV	V2	TV	V1	TV	V2	TV	V1	TV	V2	TV	V1	TV	CV	TV
VIPP-FI and AC	CF	GB	F1	F2	F3	V3	F1	F2	F3	V3	F1	F2	F3	V3	F1	F2	F3	GB	CF

*Note*. *RE* Repeated exposure, *COMBI* Repeated exposure and VIPP-Feeding infants combined, *VIPP-FI* VIPP-Feeding infants, *AC* Attention-control, *TV* Target vegetable (either green beans or cauliflower), *CV* Control vegetable (either green beans or cauliflower); *V1* Spinach, *V2* Broccoli, *CF* Cauliflower, *GB* Green beans, *F1* Apple, *F2* Pear, *F3* Banana; *V3* Carrot

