## VIPP-feeding infants (VIPP-FI)

The VIPP-Feeding Infants intervention focuses on *how* to feed an infant. The intervention is based on an existing parenting intervention that has repeatedly been proven effective in enhancing both parental sensitivity in general and sensitive discipline in particular: the Video-feedback Intervention to promote Positive Parenting-Sensitive Discipline (VIPP-SD) [84]. For the present study, the VIPP-SD was adapted to the specific situation of feeding infants (VIPP-FI) and aims to enhance sensitive parenting during feeding. The intervention consists of five sessions that take place at home and makes use of a detailed protocol that can be requested from the first author, SV. To avoid overlap with the RVE intervention, interveners are explicitly not allowed to give any advice on what type of food to give the infant. If mothers have any specific questions about this, they are referred to their youth health care center or the Dutch Nutrition Centre.

The goal of VIPP-FI is to increase mothers’ sensitive reactions to her child’s hunger and satiety cues and to increase sensitive discipline and autonomy support during feeding. To reach this goal, mothers are shown videotapes of their own feeding-interaction with their infant and receive feedback on these tapes by a trained intervener. For each session a different type of meal-setting is filmed. The videos also include potentially challenging situations like introducing the child to a new taste. The mealtimes are filmed approximately one week before the session takes place, to allow the intervener to prepare the feedback they want to give mothers. The different settings that are filmed and topics that are discussed during each session are displayed in Table 4.

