## Vegetable exposure + VIPP-feeding infants (COMBI)

Participants randomly allocated to the combined intervention receive both the RVE intervention and the VIPP-FI as described above. Similar to these interventions, families receive five phone calls for the RVE intervention and five home visits for VIPP-FI, at the same moments as in the two separate interventions.

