## Discussion

*Baby’s First Bites* will be the first trial explicitly testing the separate and combined effects of promoting the *what* and *how* of complementary feeding. By comparing three prolonged, intensive interventions, we will be able to draw firm conclusions on what is most important to focus on when promoting vegetable acceptance and children’s self-regulation of energy intake in early childhood; what food to offer, how to offer this food, or a combination of the two. Moreover, this will be the first trial to include an intervention specifically manipulating sensitive feeding practices without manipulating any other variables, evaluating its effects using both self-report and observational measures. This allows conclusions on whether this parenting practice will indeed promote healthier food preferences in children and will foster children’s ability to self-regulate their energy intake, as is often suggested in the literature.

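### The number of contacts is not the same in all conditions: the combined arm has twice the intervention sessions of every other arm, and VIPP-FI is matched to the control in number but not in mode

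*Protocol article*

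**What the plan says.** The Interventions section gives a purpose and then a design property. The purpose is "To control for possible placebo-effects due to receiving attention from researchers/interveners". The property is that "the number of contacts with researchers/interveners and time in between contacts are the same for all conditions". The Abstract (Methods) agrees: "All mothers participate in five sessions spread over the first year of eating solid foods".

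The arm descriptions give the detail:

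- **AC:** five phone calls (Table 1; section on the attention control condition).
- **RVE:** five phone calls (Table 1).
- **VIPP-FI:** five home visits with video feedback (Table 1). The Discussion puts a visit at 60 to 90 minutes.
- **COMBI:** "families receive five phone calls for the RVE intervention and five home visits for VIPP-FI". Table 2 lists a call and a visit together at each session time. The Discussion adds that two different people delivered the two parts and that the RVE content was deliberately kept out of the visits.

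On the control, Aims and hypotheses refers to "the control condition without guidance on complementary feeding". The section on the feeding schedule in all groups says that "mothers receive a printed overview of the feeding schedule indicating which puree to feed their child on each of the 19 days", and this applies to AC mothers too.

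**The concern.** An attention control protects a contrast only if the two arms receive comparable attention. The article says they do. A reader would rely on that sentence to rule out the explanation that a better result simply reflects more time with an interested professional.

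The contrasts at stake carry most of the hypotheses. Hypothesis (c) compares COMBI with each single intervention. Hypothesis (b) sets the two arms with intervention home visits against the two phone-only arms. Two of the three comparisons with control under hypothesis (a) also involve VIPP-FI or COMBI.

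Mothers are not blinded, and several primary outcomes come from them: vegetable liking, the eating-behaviour questionnaires, and the 24-hour recalls from 12 months on. The Discussion nevertheless expects firm conclusions on whether the what, the how or the combination matters most.

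**Working it through.** **Inputs.** Sessions per arm come from Tables 1 and 2 and the COMBI and AC sections. Visit length (60 to 90 minutes) comes from the Discussion. Shared assessment visits come from the feeding-schedule and Measures sections: days 1, 2, 18 and 19, plus one visit each at t12 and t18, so 4 + 2 = 6. The five planned contrasts come from Analyses.

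**Step 1: reproduce the stated figure.** The plan's figure is an equal number in all arms, five sessions each. The count gives five in AC, RVE and VIPP-FI. It gives 5 + 5 = 10 in COMBI. The figure is not reproduced for COMBI.

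**Step 2: contacts and visit time per arm, to t18.** Intervention-visit time = visits × 60 to 90 minutes; 5 × 60 = 300 and 5 × 90 = 450.

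| Arm | Calls | Intervention visits | Sessions | Shared visits | Total | Intervention-visit time |
|---|---|---|---|---|---|---|
| AC | 5 | 0 | 5 | 6 | 11 | 0 min |
| RVE | 5 | 0 | 5 | 6 | 11 | 0 min |
| VIPP-FI | 0 | 5 | 5 | 6 | 11 | 300–450 min |
| COMBI | 5 | 5 | 10 | 6 | 16 | 300–450 min |

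The ratio of COMBI to any other arm is 10/5 = 2.0 for intervention sessions and 16/11 ≈ 1.45 for all contacts counted here. The totals are minimums. Any further contact common to all arms would raise both counts and leave the difference of five unchanged. Call length is not given, so total minutes cannot be compared.

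**Step 3: the five planned contrasts.**

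| Contrast | Sessions | Mode | Result |
|---|---|---|---|
| RVE v AC | 5 v 5 | calls v calls | matched in number and mode |
| VIPP-FI v AC | 5 v 5 | visits v calls | number matched; mode and length not |
| COMBI v AC | 10 v 5 | calls and visits v calls | number and mode not matched |
| COMBI v RVE | 10 v 5 | calls and visits v calls | number and mode not matched |
| COMBI v VIPP-FI | 10 v 5 | calls and visits v visits | five extra calls |

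**Step 4: spacing.** The COMBI and AC sections both place contacts at the same times as in the other arms, and Table 2 agrees. The statement about time between contacts holds for every arm.

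**The case against.** The best defence is that COMBI calls and visits fall at the same moments, so each arm has five contact occasions, and five sessions in the Abstract could mean that. This stands for spacing. It does not stand for number: the calls and visits are separate events with different people, and the article explains why they were not merged.

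A second defence is that the sentence promises equal number and spacing, not equal mode or length. That is right. A reader might infer that all four unmatched contrasts contradict the sentence, but VIPP-FI against AC is 5 against 5 and satisfies it literally. Home contact is also inherent in video feedback. What weakens there is the purpose of the sentence, not its truth.

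Third, the Discussion already concedes that COMBI may really be two interventions, names the two deliverers and gives the visit length. It does not connect any of this to unequal attention.

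Three further inferences are tempting and not supported:

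- That filming adds visits. The VIPP-FI section says "The mealtimes are filmed approximately one week before the session takes place" but not who films, so nothing is counted for it.
- That the Discussion claims matched contact when it describes a test of sensitive feeding "without manipulating any other variables". In context this sets VIPP-FI apart from earlier trials that bundled several kinds of advice.
- That AC infants start on fruit alone. Table 3 gives them cauliflower and green beans on days 1, 2, 18 and 19.

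Finally, not every outcome rests on the mother's report. Researchers weigh intake on those four days and run the eating-in-the-absence-of-hunger procedure, and the coders of the videos are blinded.

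**Conclusion.** The equal-number statement is false for the three COMBI contrasts: 10 against 5 intervention sessions, or at least about 16 against 11 with the shared visits to t18. VIPP-FI against AC is matched in number and spacing but compares 5 to 7.5 hours of home visits with phone calls, so attention is only partly controlled. RVE against AC is the one contrast matched in number and mode.

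The counts assume that a call and a visit at the same session time are two contacts, which the delivery by two people supports, and that t12 and t18 each involve one home visit. The documents give no size for an attention effect. They therefore do not show that any result would be due to attention, only that four of the five contrasts cannot fully separate content from amount or type of contact. The exposure is greatest for mother-reported outcomes.

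The description of the control as lacking guidance is a smaller wording matter. AC callers give no feeding advice, but AC mothers follow a supplied 19-day schedule.

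**What to change.** 1. In Interventions and the Abstract, replace the equal-contacts and five-sessions statements with the contacts per arm. State that timing is matched in all arms, that number is not matched for COMBI, and that mode is not matched for VIPP-FI or COMBI against the phone-only arms.
2. Interpret COMBI v AC, COMBI v RVE, COMBI v VIPP-FI and VIPP-FI v AC as the effect of content plus additional or face-to-face contact. Qualify the firm conclusions promised in the Discussion accordingly, especially for mother-reported outcomes.
3. Report the number of sessions delivered by arm. Report contact time only if it was recorded: the article describes interaction notes for RVE and VIPP-FI, mentions none for AC, and nowhere says that minutes are logged.
4. In Aims and hypotheses, describe AC as receiving no advice on complementary feeding from the callers while following a supplied 19-day schedule of mainly fruit and carrot, with cauliflower and green beans on days 1, 2, 18 and 19.

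Inclusion is complete and no arm needs to change. The cost is some rewording and one descriptive table. The downside is a narrower claim about the how and the combination.

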## All groups/conditions

### Feeding schedule and provision of foods in all groups

Prior to the start of each intervention, all mothers are instructed to give their infant rice-flour porridge with a spoon for at least five days, to accustom the infant to eating food from a spoon [26]. Each intervention starts with providing infants their first bites of complementary foods according to a specific 19-day feeding schedule (see Table 3). The infants in the repeated exposure and combined conditions receive a variety of commercially available jars of vegetable purees, whereas the infants in the VIPP-FI and attention-control condition receive similar jars containing both fruits and a sweet vegetable puree (carrots). During the first two days and the last two days of the feeding schedule, the target and control vegetables (cauliflower and green beans) are provided to infants in all conditions. During these days, families are visited at home by the research team and the feed is videotaped; researchers measure at home how much the child has eaten (see *Measures*). During the other days of the feeding schedule, the mother feeds her child at home without the presence of the researchers. To facilitate compliance to the feeding schedule, mothers receive a printed overview of the feeding schedule indicating which puree to feed their child on each of the 19 days. In addition, each jar of food is labelled with a sticker indicating the day of the feeding schedule.

**Table 3 Tab3:** Feeding schedules used within each intervention group and the control group

	Day																		
Condition	1	2	3	4	5	6	7	8	9	10	11	12	13	14	15	16	17	18	19
RE and COMBI	TV	CV	TV	V1	TV	V2	TV	V1	TV	V2	TV	V1	TV	V2	TV	V1	TV	CV	TV
VIPP-FI and AC	CF	GB	F1	F2	F3	V3	F1	F2	F3	V3	F1	F2	F3	V3	F1	F2	F3	GB	CF

*Note*. *RE* Repeated exposure, *COMBI* Repeated exposure and VIPP-Feeding infants combined, *VIPP-FI* VIPP-Feeding infants, *AC* Attention-control, *TV* Target vegetable (either green beans or cauliflower), *CV* Control vegetable (either green beans or cauliflower); *V1* Spinach, *V2* Broccoli, *CF* Cauliflower, *GB* Green beans, *F1* Apple, *F2* Pear, *F3* Banana; *V3* Carrot

After this feeding schedule has been completed, all families are provided with a total of 100 jars of age-appropriate fruits and/or meals with vegetables, depending on the condition they are in, up until the child is approximately 12 months of age (distributed on five different occasions; 20 jars per occasion). Parents are free to decide whether they want to feed their baby using homemade foods or the jars provided to them. The provision of these foods serves as a means to facilitate prolonged exposure to vegetables in the repeated vegetable exposure conditions by making sure age-appropriate meals containing vegetables are available to the families. Whether or not families use these jars and how much the child eats of these jars is reported by the mother.

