	Enrolment	Intervention-period						Post-test	Follow-up	
Child age (in months)	2–4	4–7		8	12	13	16	18	24	36
Time point		*t* _*0*_	*t* _*1*_		*t* _*12*_			*t* _*18*_	*t* _*24*_	*t* _*36*_
Enrolment & allocation										
1. Invitation e-mail	x									
2. Information and informed consent	x									
3. Screening	x									
4. Allocation	x									
5. Rice-flour porridge	x									
Interventions										
RVE										
Feeding schedule		days 1–19								
Phone-call		Twice in period days 3–17		x		x	x			
Provision of vegetable purees		X		x	x					
VIPP-FI										
Feeding schedule		days 1–19								
Home-visit		Twice in period days 3–17		x		x	x			
Provision of fruit and carrot purees		X		x	x					
Combined RVE + VIPP-FI										
Feeding schedule		days 1–19								
Phone-call + home-visit		Twice in period days 3–17		x		x	x			
Provision of vegetable purees		X		x	x					
Attention-control										
Feeding schedule		days 1–19								
Phone-call		Twice in period days 3–17		x		x	x			
Provision of fruit and carrot purees		X		x	x					
Assessment of study outcomes^a^		Days 1 + 2	Days 18 + 19		x			x	x	x

*Note.*
^a^Primary outcomes: vegetable intake and liking, child self-regulation of energy intake. Secondary outcomes: child anthropometrics, child eating behavior and maternal feeding behavior. RVE = repeated exposure to vegetables. VIPP-FI=Video-feedback Intervention to promote Positive Parenting-Feeding Infants

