#### Other measures

The following potential covariates will be assessed: demographic variables such as maternal and paternal education and job status, family income, cultural background (*t*_*0*_); type of milk feeding (breast/formula: *t*_*0*_*-t*_*18*_); maternal depression (*t*_*0*_*-t*_*36*_: Center for Epidemiologic Studies Depression Scale [101]); maternal vegetable intake (*t*_*12*_ and *t*_*36*_: Food frequency questionnaire [102]); maternal anthropometrics (*t*_*0*_*-t*_*36*_); use and amount of purée consumed of the 100 distributed vegetable- and fruit jars in the 5 months after the feeding schedule (*t*_*12*_); maternal self-efficacy related to feeding their child (*t*_*0*_*-t*_*36*_: Parental Feeding Self-Efficacy Questionnaire [103]); maternal emotions during feeding the child (*t*_*0*_*-t*_*36*_: measure designed for this study); structure of family meals (*t*_*0*_*-t*_*36*_: Meals in our Household [104]); maternal perception of feeding (*t*_*0*_*-t*_*36*_: Five Minute Speech Sample [105]); child temperament (*t*_*0*_*-t*_*12*_: Infant Behavior Questionnaire-Revised [106]; *t*_*18*_*-t*_*36*_: Early Childhood Behavior Questionnaire [107]); general parenting styles (*t*_*0*_*-t*_*36*_: observed maternal intrusiveness during mealtimes and observed maternal sensitivity and intrusiveness during free-play situations [95]; *t*_*18*_*-t*_*36*_: Comprehensive General Parenting Questionnaire [108]).

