### Analyses

The intention-to-treat principle will be applied to all analyses. Whether the interventions differentially affect primary and secondary outcomes over time will be analyzed using linear mixed models analyses, a technique that makes use of every data point for every participant, irrespective of their missing data. The three intervention groups will be compared to the control group, and the combined group will be compared to the repeated exposure and the VIPP-FI group. A significance level of α = .05 will be used. The analyses will be corrected for relevant covariates such as family socioeconomic status, maternal consumption of vegetables, parental body mass index (BMI), child temperament, etc.

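### Intake from the study jars, a post-randomization measure of uptake, is listed as a potential covariate; adjusting for it is permitted and would break the intention-to-treat contrasts between vegetable-jar and fruit-jar arms

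*Protocol article*

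**What the plan says.** All places are in the protocol article.

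- **Feeding schedule and provision of foods in all groups.** After the 19-day schedule each family receives 100 jars: "age-appropriate fruits and/or meals with vegetables, depending on the condition they are in". Their purpose is stated: "The provision of these foods serves as a means to facilitate prolonged exposure to vegetables in the repeated vegetable exposure conditions". Use is optional and is reported by the mother.
- **Table 2.** Jar provision is listed under each arm's intervention. For RVE and COMBI the row reads "Provision of vegetable purees"; for VIPP-FI and AC it reads "Provision of fruit and carrot purees".
- **Other measures.** The list opens with "The following potential covariates will be assessed" and includes, at t12, "use and amount of purée consumed of the 100 distributed vegetable- and fruit jars in the 5 months after the feeding schedule".
- **Analyses.** Intention to treat applies to all analyses. Then: "The analyses will be corrected for relevant covariates such as family socioeconomic status, maternal consumption of vegetables, parental body mass index (BMI), child temperament, etc". The three interventions are compared with AC, and COMBI is compared with RVE and with VIPP-FI.

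**The concern.** A covariate in a randomized comparison should be something that allocation cannot have changed. Jar intake fails this test. It is recorded at t12, months after randomization. What is in the jars is set by the arm, and how much is eaten can respond to the advice the mother receives. In RVE and COMBI, eating the jars is one of the ways in which the intervention is meant to work.

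If jar intake is held constant in the model, the arm coefficient compares infants who ate the same amount from jars containing different foods. That is not the effect of being assigned to the intervention, and appetite, which can drive both jar intake and the outcomes, adds a further distortion. The contrasts at stake are the three that set vegetable jars against fruit and carrot jars: RVE versus AC, COMBI versus AC and COMBI versus VIPP-FI. They carry the trial's question about what to feed. COMBI versus RVE and VIPP-FI versus AC share a jar type, but the variable is post-randomization there too. For the t1 outcomes, measured on days 18 and 19, the adjustment would be for something that happens later.

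**Working it through.** **1. Does the text permit the adjustment?** Other measures calls the variable a potential covariate. Analyses corrects for relevant covariates, gives four examples and leaves the list open. Jar intake is neither named nor excluded, and no rule limits covariates to baseline. One of the four named examples, maternal vegetable consumption, is itself measured only at t12 and t36 according to Other measures. So the text does not screen out post-randomization variables.

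**2. Is jar intake on the intended path?** The section on the RVE intervention sets daily vegetable offering after the first 19 days as a goal and names availability of vegetables as a targeted determinant. The jars are said to serve prolonged exposure in those arms. Intake from them is therefore a measure of uptake.

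**3. The plan's own sample size, as a reference.** For effect size 0.50, power 0.80 and alpha 0.05, n per group = 2(z_alpha + z_beta)²/0.50².

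- Two-sided: 2(1.960 + 0.842)²/0.25 = 62.8, so 63 (64 by t-test).
- One-sided: 2(1.645 + 0.842)²/0.25 = 49.5, so 50 (50.15 by t-test, so 51).

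The stated 51 is reproduced one-sided. Two-sided power with 51 per arm is 0.71. Sidedness is a separate matter; 51 per arm is used here only as the reference size.

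**4. What adjustment would do.** With one common slope for jar intake, the expected adjusted arm effect is

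adjusted effect = total effect − a × s,

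where a is the difference between arms in jar intake (in SD) and s is the pooled within-arm slope of the outcome on jar intake.

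The documents give neither a nor s. Assumed: slope 0.3 or 0.5 in the vegetable-jar arm; 0 or 0.3 in the fruit-jar arm; a shared appetite factor with loading 0 or 0.4 on both intake and outcome, which adds 0.4² = 0.16 to the slope. The six combinations examined give s from (0.3 + 0)/2 = 0.15 to (0.3 + 0.3)/2 + 0.16 = 0.46. With a total effect of 0.50 SD, the simulation used 51 per arm, 2,000 runs per setting and a two-sided 0.05 test:

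| a (assumed) | 0.50 − a × s | Simulated adjusted estimate | Simulated power, adjusted |
|---|---|---|---|
| −0.5 | 0.58 to 0.73 | 0.58 to 0.73 | 0.82 to 0.99 |
| 0 | 0.50 | 0.49 to 0.50 | 0.73 to 0.87 |
| +0.3 | 0.36 to 0.46 | 0.36 to 0.45 | 0.51 to 0.67 |
| +0.5 | 0.27 to 0.43 | 0.28 to 0.42 | 0.32 to 0.56 |
| +0.8 | 0.13 to 0.38 | 0.14 to 0.38 | 0.11 to 0.44 |

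Without jar intake in the model, the estimate stays at about 0.50 in every setting, with power of about 0.69 to 0.81. The sign of the bias follows the sign of a, and the bias vanishes at a = 0.

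**The case against.** **Adjustment is not planned.** A reader might infer that the models will be corrected for jar intake. The text does not say so: the list is of potential covariates, and Analyses does not name this one. Choosing the final set is commonly left to a statistical analysis plan. This stands, and it limits the point. What remains is not an omission: the protocol itself files an uptake measure alongside demographics and temperament as a candidate for adjustment.

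**The jars are not the intervention.** They go to all arms, use is optional, they also appear as participant compensation, and the RVE section says that the determinants are targeted through the feeding schedule and the calls. It is fair that jar intake is not the whole delivered dose. The stated purpose of the jars and their place in Table 2 still put it on the intended path.

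**The foods are not opposites.** Carrot is a vegetable, and nothing says that a single pooled amount would be modelled. Both are correct; the common slope above is an assumption. The main objection to a post-randomization covariate does not depend on it.

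Two stronger readings are tempting and not supported:

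- *Jar intake is partly the outcome itself.* Intake at t1 is weighed on days 18 and 19, before the 100 jars are supplied. Later intake comes from recalls whose invitations follow the home visits at t12 and after. The recording window closes on average at 4.68 + 19/30.44 + 5 = 10.3 months, and for the oldest starter at 6.38 + 0.62 + 5 = 12.0 months. Recorded jar intake thus largely precedes the recalls.
- *Part of the supply period goes unrecorded.* Supply ends at approximately 12 months, and the upper end of the t1 age range plus five months is 7 + 5 = 12. The five months can also be read as describing when jars were distributed. This is loose wording with no bearing on intention to treat.

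**Conclusion.** The point holds as a fault in how the protocol classifies one variable. Jar intake is a post-randomization uptake measure on the intended causal path, its content differs by arm, and the protocol leaves it open as an adjustment variable while claiming intention to treat. If used, it would change what three of the five planned contrasts estimate.

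The size cannot be determined from the documents. The range of 0.14 to 0.73 SD around a true 0.50 SD rests wholly on assumed arm differences and slopes. A reader might infer that adjustment must strip out the RVE effect; it may equally inflate it, or leave it unchanged if arms eat equal amounts. The change is worth making because it costs nothing and protects the comparison the trial is built on.

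**What to change.** 1. Remove use and amount of the study jars from the list of potential covariates in Other measures, and describe it there as a measure of intervention uptake.
2. In Analyses, state that the outcome models adjust only for variables measured at baseline, including the minimization factors (age at start of complementary feeding, child gender, study location), and not for jar intake. Under this rule maternal vegetable consumption, measured only at t12 and t36, also leaves the outcome models, and temperament enters with its t0 value.
3. Report jar intake by arm, with vegetable jars and fruit or carrot jars counted separately.
4. Label any analysis of dose as exploratory and confine it to RVE and COMBI.

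The cost is wording only: no new data, no added visits and no change to sample size. If an analysis plan already restricts covariates to baseline, the protocol text needs only to be aligned with it.
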